## Abstract

**Introduction:**

The interaction between the gut microbiota and the host immune system is implicated in the pathogenesis of inflammatory bowel disease, including ulcerative colitis (UC). Targeting the gut microbiota with faecal microbiota transplantation (FMT) from a healthy donor has shown promise in inducing remission in patients with active UC. However, mixed results and protocol heterogeneity have limited its practical application. Our previous Transfer of Faeces in Ulcerative Colitis; Restoring Homeostasis (TURN) trial found a correlation of clinical response with specific strains and butyrate production. Since most gut microbes, including many butyrate producers, are anaerobes, anoxic processing of donor stool may be essential to increase efficacy of FMT in UC. This trial aims to enhance FMT efficacy by applying strict anoxic processing, selecting donors based on microbial composition and using repetitive dual-route administration.

**Methods and analysis:**

This randomised, double-blind, placebo-controlled, multicentre study evaluates the efficacy of strictly anoxic prepared donor FMT compared with anoxic prepared autologous FMT in patients with mild to moderate active UC. An open-label extension option is available for non-responders in the autologous arm. Included patients will receive 4 weekly FMTs, comprising two double-route administrations (nasoduodenal administration combined with enema) and two single enemas. Donors are selected based on their microbiota profile, informed by our previous TURN trial and literature. A total of 76 patients evaluable for the primary endpoint will be included. The primary endpoint is steroid-free clinical and endoscopic remission at week 8, assessed by the adapted Mayo score. An interim analysis will be conducted midway through the study by a Data Safety Monitoring Board to monitor efficacy and safety. Other outcomes of this study include the evaluation of clinical, endoscopic and histological response. In addition to clinical results, this study aims to provide valuable insights into specific microbial strains, metabolites and mechanisms correlated with response, aiding in the development of future microbial therapies.

**Ethics and dissemination:**

Ethics approval was obtained from the medical ethics committee of the Amsterdam University Medical Centre in the Netherlands (reference number 2018_057). All participants will provide written informed consent. The results of the trial will be disseminated through publication in a peer-reviewed journal and presentations at (inter)national conferences.

**Trial registration number:**

Prospectively registered in May 2018 in the Dutch Trial Register (NTR/LTR) as NL7770. Assigned NL-OMON52507 following the transition of the Dutch Trial Register to the Overview of Medical Research in the Netherlands. Also registered at ClinicalTrials.gov (NCT05998213).

STRENGTHS AND LIMITATIONS OF THIS STUDYThis is one of the first multi-centre trials applying anoxic processed faecal microbiota transplantation (FMT) from microbiota-selected faeces donors, with a long follow-up period of 1 year.In addition to evaluating the efficacy of this adjusted FMT protocol, the study will provide insights into FMT’s mechanism of action via microbiome and metabolome analyses.A blinded critical event committee is established to enhance reliability of the primary endpoint.Health-related quality of life and fatigue will be assessed.Our findings may not be generalisable to other countries, as all participants were recruited in the Netherlands.

## Introduction

 Ulcerative colitis (UC) is a chronic inflammatory bowel disease (IBD) affecting millions of people worldwide, with a continuingly rising incidence.^1^ Symptoms such as abdominal pain and bloody diarrhoea typically begin in adolescence and lead to life-long substantial morbidity with high associated costs.^1 2^ Current available treatments, including immunosuppressants, immunomodulators and expensive biologics, have an efficacy ceiling of around 30% after 1 year^3^ and are accompanied by potential serious side effects.^4^ Thus, the development of more efficacious and safe treatments is paramount.

The pathogenesis of UC is incompletely understood but involves inappropriate activation of the mucosal immune system, likely driven or maintained by the intestinal microbiota.^1^ Accumulating evidence indicates that patients with UC have an altered gut microbiota composition compared with healthy controls.^5 6^ This altered ecosystem can be targeted with several strategies, including faecal microbiota transplantation (FMT). FMT is highly efficacious for treating recurrent *Clostridioides difficile* infections.^7^ Since this reported treatment success, FMT has been investigated for various other indications, including UC.^8^

At the time of setting up this protocol, four RCTs had been published on FMT in patients with UC with active disease.^9^,^12^ The first published RCT, the Transfer of Faeces in Ulcerative Colitis: Restoring Homeostasis (TURN) trial,^9^ was a phase 2a proof-of-concept trial conducted by our group. This trial found no statistically significant difference in clinical and endoscopic remission between patients who received two fresh nasoduodenal donor FMT infusions (30.4%) compared with those who received infusions with autologous FMT (20.0%). However, in-depth microbiota analysis of recipients and donors revealed interesting findings related to clinical outcomes.^9 13^

Response was associated with a microbial composition shift towards the donor’s profile, including increase of alpha-diversity and restoration of *Clostridium* clusters IV, XIVa and XVIII, which belong to the *Firmicutes* (currently renamed to *Bacillota*) phylum.^13^ Sustained remission (⩾1 year) was linked to known butyrate-producing bacteria and overall increased butyrate production capacity, as assessed through functional predictions and targeted quantitative PCR (qPCR).^13^ Butyrate, a short chain fatty acid (SCFA),^14^ is primarily produced by species within the Firmicutes phylum (currently renamed to *Bacillota*)^15^ and is known to downregulate proinflammatory responses in intestinal epithelial cells and to support the gut barrier function.^14^ In contrast, non-response and relapse were associated with increased levels of *Proteobacteria* (currently renamed to *Pseudomonadota*) in patients’ baseline samples and high levels of bacteria that are phylogenetically related to the mucus degrader *Ruminococcus gnavus*^16^ in donors.

Three subsequent published RCTs^10^,^12^ reported a significant treatment effect of FMT ranging between 24 and 32%, compared with placebo rates of 5 to 9%. FMT protocols varied greatly regarding the number of infusions, route of administration, single vs multidonor approach and processing techniques. Microbiota analysis of these trials showed an association of response with several factors, including Clostridium cluster IV, XVII and potential butyrate-producing bacteria,^11 12^ similar to the TURN trial results. Remarkably, a Canadian trial by Moayyedi *et al*,^12^ revealed a highly efficacious donor responsible for seven out of nine responders, suggesting a donor-dependent effect. This donor was particularly rich in *Lachnospiraceae* and *Ruminococcus*.

The majority of the gut microbiota consists of oxygen-sensitive bacteria,^17^ under which butyrate producers. Therefore, regular applied aerobic processing techniques of donor stool diminish the bacterial viability of obligate anaerobes compared with strict anoxic processing, as recently published by our group.^18^ An Australian trial by Costello *et al*^10^ used anoxic processing and reported that the bacteria most strongly associated with clinical response were obligate anaerobes.^10^

In line with current guidelines,^19 20^ we use frozen FMT as clinical efficacy does not appear to be negatively affected by a freeze-thaw cycle,^21^ while using frozen samples offers practical advantages and enhances safety by applying quarantine periods before release of FMT syringes until negative donor rescreening.

We hypothesise that in our follow-up TURN2 trial, we can boost treatment efficacy of FMT in patients with UC with mild to moderate disease by:

Applying donor selection based on microbiota profile.Using strict anoxic faecal processing to retain viable oxygen-sensitive bacteria, including many butyrate producers.Combining nasoduodenal and rectal administration with proper bowel cleansing to enhance engraftment.

### Objective

This study aims to investigate the efficacy and safety of FMT augmented by donor selection, anoxic faeces processing and repetitive dual-route administration for the treatment of UC.

### Trial design

The TURN2 trial is a randomised, double-blind, placebo-controlled, multi-centre, parallel-group phase 2 trial with open-label extension option for non-responders in the placebo arm. Eligible patients will be randomised to receive anoxic donor FMT or anoxic autologous FMT in a 1:1 allocation ratio.

## Methods and analysis

### Participants, interventions and outcomes

#### Study setting

Two academic hospitals in the Netherlands are participating. The main study centre is the Amsterdam University Medical Centre (UMC), where all study participants are screened and sigmoidoscopies are performed. All other study visits, including the administration of FMTs, are conducted either at the Amsterdam UMC or at the University Medical Center Groningen (UMCG).

#### Study population

Patients diagnosed with UC with mild to moderate disease activity.

### Eligibility criteria

#### Inclusion criteria patients

Adults aged ≥18 and <70 years at the time of inclusion.Established UC according to the Lennard-Jones criteria^22^ with known involvement of the left colon.Partial Mayo score of ≥3.Faecal calprotectin >250 µg/g.Full Mayo score of 5–9.Endoscopic Mayo score of ≥2 in either the rectum or sigmoid on screening sigmoidoscopy.No or stable dose of thiopurines and/or mesalamines in the preceding 8 weeks.No or stable dose of budesonide in the preceding 2 weeks.No prednisone use or prednisone ≤15 mg/day in the preceding 2 weeks with a mandatory taper of 5 mg per week starting from week 4.Ability to give informed consent.

#### Main exclusion criteria patients

Crohn’s disease.Condition leading to profound immunosuppression.Use of anti-tumour necrosis factor-α treatment, integrin antagonists, Janus kinase inhibitors, ustekinumab (monoclonal antibody) and/or methotrexate in preceding 2 months.Use of systemic antibiotics and/or probiotics in preceding 4 weeks.Use of topical therapy (5-aminosalicylic acid/mesalamine and/or steroids) in the preceding 2 weeks.Positive stool cultures for common enteric pathogens (eg, *Salmonella, Shigella, Yersinia, Campylobacter,* Enteropathogenic *Escherichia coli*).Positive *C. difficile* stool test.Positive dual faeces test for pathogenic parasites (eg, *Dientamoeba histolytica*, *Giardia lamblia*, *Dientamoeba fragilis* and/or *Blastocystis* spp. In the case of the presence of *Blastocystis* spp only exclusion if many or very many *Blastocystis* spp. are seen microscopically).

The complete list of exclusion criteria is provided in online supplemental file 2.

#### Donors

Potential donors are recruited by advertising among employees of the Amsterdam UMC and preclinical medical students. The screening protocol is based on that of the Netherlands Donor Feces Bank^23^ and is in accordance with the 2019 European clinical consensus report.^24^ It has been updated according to new insights and risks,^25^,^27^ including the COVID-19 pandemic. A detailed description of the donor screening process, donor acceptance rates and feasibility has been published recently.^28^ Eligible donors are asked to donate for a period of a maximum of 12 weeks. Rescreening is conducted after 4 weeks after a donation period to account for window periods to detect certain viruses. Only after successful rescreening are quarantined FMT syringes from that particular donation period are released. Donors are offered a modest amount of money and coffee/lunch vouchers for the hospital café per ten donations. Screening criteria and screening timelines are listed in online supplemental tables 3 and 4 and online supplemental figure 1.

#### Inclusion criteria donors

Adults aged ≥18 and <55 years at the time of inclusion.BMI ≥18.5 and ≤26 kg/m².Recruited donors are ranked based on expected beneficial microbiota profile. Arbitrarily, the highest 50% of average-ranked donors are included in the study. The following criteria are used for selection: high alpha diversity (assessed using Faith’s phylogenetic diversity), high predicted butyrate production (based on specific genera abundance, qPCR or inference using Phylogenetic Investigation of Communities by Reconstruction of Unobserved States [PICRUSt]), inverse relative abundance of *Ruminococcus gnavus*, inverse relative abundance of Proteobacteria and overall profiles that resemble successful TURN donors (assessed using Weighted UniFrac).Ability to give informed consent.

#### Exclusion criteria donors

Extensive exclusion criteria for faeces donors are listed in online supplemental table 5.

### Interventions

#### Faecal microbiota transplantation

Patients receive FMT weekly for 4 weeks (figure 1 and online supplemental table 1). Each treatment involves the administration of a 200 mL retention enema. The first and last treatments (week 0 and week 3) consist of dual-route administration, which includes nasoduodenal administration of 300 mL FMT via a CORTRAK* Enteral Access System (Avanos Medical, Alpharetta, USA) and a retention enema. To enhance engraftment, bowel lavage is performed with 3 L macrogol electrolytes solution (Moviprep) beforehand. Patients may choose to either drink the solution or administer it via the CORTRAK tube, which is then placed 1 day before the treatment (visit 2). We added this option to accommodate patients who have difficulty drinking the bowel lavage. In both cases, the bowel lavage is performed at home.

**Figure 1 F1:**
[figure not shown]
Schematic overview of the study design. FMT, faecal microbiota transplantation.

On days when only a retention FMT enema is administered (week 1 and week 2), bowel preparation consists of a sodium chloride (NaCl) enema. NaCl enemas are used instead of phosphate-containing enemas, as the latter can influence the results of microbiota analysis. To increase retention time, loperamide 4 mg is given orally 30 min to 1 hour before FMT administration.

At each FMT visit, a trained nurse or physician is present to provide guidance and reassurance during nasoduodenal placement and/or enema administration. The volume of bowel preparation ingested and the completeness of FMT administration are recorded, and any incomplete intake is documented as a protocol deviation. Patients are encouraged to retain the enema for as long as comfortably possible, and retention time is recorded. Discomfort related to the nasoduodenal tube or rectal administration is assessed at every visit, and symptoms are registered as adverse events (AEs) when applicable.

#### Investigational product

Donor faeces is collected (minimum 20 grams) in an allocated toilet in the Amsterdam UMC in a plastic container placed in a vacuum box (10006101;0 from ALLPAX). Immediately after donation, AnaeroGen sachets (Anaerogen Compact, Thermo Fisher) are added as oxygen scavenger and the container is evacuated to a 97% vacuum. The donation is then transferred to an anaerobic chamber (Anaerobic workstation Concept 500, Baker Ruskin) within 30 min for further processing. This collection and transfer protocol was adjusted from An *et al*,^29^ who demonstrated that their approach facilitated the survival of obligate anaerobes using propidium monoazide (PMA) and culturing. Inside the anaerobic chamber, the stool is weighed and homogenised with NaCl 0.9% in a ratio of 1:3.3–5.5 (depending on consistency) using a blender with a steel autoclavable container (Warring 1LB20ESA). The solution is then filtered using a metal autoclavable tunnel and gauze. Cryoprotectant glycerol (85%) is added to achieve a final concentration of 10%. The prepared FMT is stored in labelled syringes covered with aluminium foil in a −70°C freezer. Before use, syringes are thawed in an anoxic box (AnaeroPack 7.0L, Mitsubishi) with AnaeroGen sachets for either 5 hours at room temperature or overnight in a refrigerator. Patients receive FMT from the same donor for each treatment, while multiple donors are employed throughout the study.

#### Control product

The control product consists of anoxic collected and prepared autologous faeces. This is collected and processed according to the same standard operational procedure. To minimise burden for patients, we collect this stool before the baseline sigmoidoscopy, spontaneously or after patients have received NaCl enema as preparation. Regular laxative enemas containing phosphate were deemed unsuitable due to their potential impact on the microbiota.^30^ The collected stool is diluted with sterile NaCl to a final volume equivalent to that of the investigational product (ie, 1400 mL for four treatments in total).

### Outcomes

#### Primary outcome

The primary endpoint is the proportion of study subjects in steroid-free clinical and endoscopic remission at 8 weeks, assessed using the adapted Mayo score, defined as:

Stool Frequency Subscore (SFS)≤1Rectal Bleeding Subscore (RBS)=0.Endoscopic subscore≤1.

The reason for choosing 8 weeks as the primary endpoint was a compromise based on observations from the FATLOSE trial, in which it was observed that the microbiota signature tends to revert to its original composition after 4 weeks,^31^ and from our previous TURN trial, where after twofold nasoduodenal administration of FMT in UC we noticed that several patients responded already within 1 week, while others only after 6 weeks.^9^ Most of the patients who achieved the primary endpoint at 12 weeks were still in clinical remission at 52 weeks.^13^

#### Secondary outcomes

Secondary outcomes include:

Proportion of patients with:Clinical response per adapted Mayo score at week 8 (ie, excluding Physician’s Global Assessment (PGA) subscore): a decrease from baseline ≥2 points and ≥30%, plus a decrease in RBS≥1 or an absolute RBS≤1.Clinical improvement per partial adapted Mayo score at week 8 (ie, excluding PGA and endoscopy subscore): a decrease from baseline ≥1 points and ≥30%, plus a decrease in RBS≥1 or an absolute RBS≤1.Full clinical remission per full Mayo score at week 8: a decrease from baseline of ≤2 points with no subscore >1.Complete remission per full Mayo score at week 8: ≤2 points reduction from baseline with no subscore >1 and a rectal bleeding score and endoscopic subscore of 0.Sustained steroid-free remission per adapted Mayo at week 8; SFS≤1, RBS=0, endoscopic subscore≤1 and no need for rescue therapy until week 52.Endoscopic complete remission at week 8: endoscopic subscore=0.Endoscopic improvement at week 8: endoscopic subscore of 0 or 1.Endoscopic response at week 8: ≥1 point reduction in summed endoscopic Mayo score (endoscopic subscore of rectum+endoscopic subscore of sigmoid).Histological remission assessed via Nancy Histological Index (NHI)^32^,^34^: NHI≤1.Change in:Simple Clinical Colitis Activity Index from baseline to week 1, 2, 3, 4, 8, 18, 39 and 52.Partial Mayo: from baseline to week 1, 2, 3, 4, 8, 18, 39 and 52.IBD-Control: from baseline to week 2, 4, 8, 18, 39 and 52.Occurrence of AEs

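### The two full-Mayo remission endpoints cap the improvement at 2 points instead of the week 8 score, so complete remission cannot be reached and true remitters count as failures

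*Protocol article*

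**What the plan says.** Two secondary endpoints in the Protocol article (Outcomes, Secondary outcomes) use the full Mayo score at week 8:

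- "Full clinical remission per full Mayo score at week 8: a decrease from baseline of ≤2 points with no subscore >1".
- "Complete remission per full Mayo score at week 8: ≤2 points reduction from baseline with no subscore >1 and a rectal bleeding score", continuing with an endoscopic subscore of 0. The complete condition is "≤2 points reduction from baseline with no subscore >1 and a rectal bleeding score and endoscopic subscore of 0".

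The entry criteria (Eligibility criteria, Inclusion criteria patients) fix where patients start: "Full Mayo score of 5–9", "Partial Mayo score of ≥3" and "Endoscopic Mayo score of ≥2 in either the rectum or sigmoid on screening sigmoidoscopy".

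The clinical response endpoint in the same list is based on the adapted Mayo score, described as "excluding Physician’s Global Assessment (PGA) subscore". It requires "a decrease from baseline ≥2 points and ≥30%, plus a decrease in RBS≥1 or an absolute RBS≤1". The full score therefore has four components: stool frequency (SFS), rectal bleeding (RBS), endoscopy and PGA. No other section of the article defines the two full-Mayo endpoints differently.

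**The concern.** A remission endpoint asks whether the patient has reached a low score. These two ask whether the score has fallen by no more than 2 points, so a large improvement disqualifies the patient. They are the only endpoints in the list with an upper limit on improvement. The response and improvement endpoints based on change set a minimum decrease, and the adapted-Mayo and endoscopic remission endpoints set absolute thresholds.

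A derivation that follows the text would report no complete remissions in either arm. It would also report a full clinical remission rate made up of patients who improved little and still have disease. If the team applies a different rule without saying so, the reported endpoint departs from the published definition, and a reader cannot tell when the change was made. Both endpoints also belong to the secondary outcomes whose p values are adjusted by Holm-Bonferroni (Statistical methods). As written, one of those tests cannot show a difference and the other does not measure remission.

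**Working it through.** The plan gives no expected rate for these endpoints, so there is no figure of its own to reproduce. The check sets the endpoint rules against the entry criteria.

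**Inputs**

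- Baseline full Mayo score *B*: 5 to 9 (Inclusion criteria patients).
- Baseline partial Mayo score at least 3 and endoscopic score at least 2 (same section).
- Week 8 full Mayo score *W* = SFS + RBS + endoscopy + PGA.
- Both endpoints as written: *B* − *W* ≤ 2 and every week 8 subscore ≤ 1. Complete remission adds RBS = 0 and endoscopy = 0 (Secondary outcomes).

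**Complete remission as written**

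1. RBS = 0, endoscopy = 0, SFS ≤ 1 and PGA ≤ 1 give *W* ≤ 0 + 0 + 1 + 1 = 2.
2. With *B* ≥ 5, *B* − *W* ≥ 5 − 2 = 3.
3. The rule requires *B* − *W* ≤ 2. The conditions contradict each other, so the endpoint cannot be met.

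**Full clinical remission as written**

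1. Four subscores of at most 1 give *W* ≤ 4.
2. *B* − *W* ≤ 2 then requires *B* ≤ 4 + 2 = 6, so patients who enter at 7, 8 or 9 can never qualify.
3. The only qualifying moves are 5 to 3, 5 to 4 and 6 to 4.
4. Any patient with *W* ≤ 2 has fallen by at least 3 and is a failure, including one who goes from 9 to 0.
5. A patient who goes from 5 to 4 with every subscore at 1, including rectal bleeding, is counted as in remission.

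**Enumeration**

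This assumes that each subscore runs from 0 to 3, which the article does not state. The assumption affects only the counts below. Of the possible baseline patterns, 94 meet the entry criteria. Each was crossed with every week 8 pattern.

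| Endpoint | Qualifying pairs as written | Qualifying pairs under *W* ≤ 2 | Pairs meeting both |
|---|---|---|---|
| Full clinical remission | 72 | 94 × 11 = 1034 | 0 |
| Complete remission | 0 | 94 × 4 = 376 | 0 |

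The 72 pairs arise as follows.

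- 5 to 3: 10 baseline patterns × 4 week 8 patterns = 40.
- 5 to 4: 10 × 1 = 10.
- 6 to 4: 22 × 1 = 22.

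Only the 5 to 3 group contains a week 8 pattern with RBS = 0, which accounts for 10 pairs. The other 72 − 10 = 62 have RBS = 1 and so fail the trial's own primary remission definition, which requires RBS = 0 (Primary outcome).

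**The case against.** The strongest reply is that the harm is conditional. The endpoint names and the condition on subscores make the intended meaning fairly plain, a 0% rate in both arms would be noticed at once, and the full protocol, which is not shown, may carry correct wording. The reach is also limited: the primary endpoint uses absolute subscores, the sample size of 38 per group rests on it, and the endoscopic and histological remission endpoints are workable. This bounds the consequence. It does not remove the error, because the article states both definitions and states them wrongly, in two differently worded sentences. That makes a lost character in the text an unlikely explanation.

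Four narrower points stand as limits:

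- **Holm-Bonferroni.** Correctly worded versions would occupy the same two places in the family. The error does not enlarge the family; it wastes two tests in it.
- **Pair counts.** 72 against 1034 counts score patterns with equal weight. These are not patients, and the ratio is not a misclassification rate. The proof for complete remission does not need them.
- **Baseline.** The impossibility assumes that the analysis baseline is the score at entry. The blinded committee reads the sigmoidoscopy videos (Data collection). If its reading defined the baseline and brought a total down to 2 + 2 = 4 or less, a patient could meet the written rule. The article describes no such baseline.
- **Intent.** That a score of at most 2 was meant is an inference. It is supported by the maximum total of 2 that the complete-remission conditions allow, but the article does not say it.

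**Conclusion.** The concern holds. With entry at 5 to 9, complete remission as written cannot be met by any eligible patient. Full clinical remission as written is open only to patients who enter at 5 or 6 and end at 3 or 4. Neither written rule is met by any patient whose week 8 full Mayo score is 2 or less.

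The conclusion for complete remission rests on the four components of the full Mayo score, the subscore limits in the endpoint, and an analysis baseline no lower than the entry minimum of 5. It does not depend on the assumed 0 to 3 range. The error must be corrected, because a prespecified endpoint that cannot occur gives no information. Its reach is two secondary endpoints; the primary endpoint and the sample size stand.

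**What to change.** Replace the two definitions and delete the references to a decrease or reduction from baseline:

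- **Full clinical remission at week 8:** full Mayo score of at most 2, with no subscore above 1.
- **Complete remission at week 8:** full Mayo score of at most 2, with no subscore above 1, and both the rectal bleeding and endoscopic subscores equal to 0. The limit on the total is then implied by the other conditions, but keeping it makes the two definitions parallel.

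The sponsor should first confirm the intended wording against the full protocol and align the derivation code with it.

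Timing needs care. Recruitment ended in November 2024 with follow-up to January 2026 (Trial status), and investigators may be unblinded once all patients have reached week 8 (Patient allocation and blinding). The article does not show whether the database has been locked. The correction should be dated, made before these endpoints are analysed if that is still possible, and reported with a statement of whether it came before or after unblinding.

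The cost is two lines of endpoint wording and the matching derivation code. No new data are needed and the sample size does not change.
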